## Stratification Factors

None

## Analysis of Primary and Secondary Endpoints

Analysis Populations

Intent-to-Treat (ITT) Population

The ITT population includes all subjects who were enrolled and treated with the combination treatment (ADT (any duration) + FT). Note: Subjects who are enrolled but not treated will be documented as screen failures. The ITT population will serve as the primary analysis set for all safety and efficacy endpoints.

Per Protocol (PP) Population

The PP population includes all subjects who were enrolled and treated with the combination treatment (ADT (any duration) + FT), and who had no major protocol deviations. The PP population will serve as a supportive analysis set for all efficacy endpoints.

Missing Data

The following imputation methods will be used for the primary analysis of all endpoints:

• When calculating the proportion of subjects with a negative biopsy for CSPCa, subjects with missing biopsy information post-ablation will be imputed as “positive”

• Missing PSA data will be imputed using last observation carried forward (LOCF) (or previous median/mean or regression-based methods if proper).

• Missing data for IIEF-5, IPSS and EPIC questionnaires will be imputed using a multiple imputation approach at the item/question level.

All other endpoints/data (e.g., safety events) will be analyzed based on available (non-imputed) data, unless specified otherwise.

Baseline demographic and clinical information will be summarized using standard summary statistics, graphs and charts (see below).

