## Subjects who do not undergo Focal Therapy or complete Focal Therapy

Any subject who has already received ADT and who for any reason is no longer a candidate for FT (e.g., if ablation of CSPCa cannot be done without damaging both neurovascular bundles, or patient withdraws consent for the procedure, or procedure is unfeasible for other reasons) the subject will be considered to be a “withdrawal” from treatment rather than a screen-failure. In the event FT is not performed or completed it will be up to the discretion of the treating investigator whether a subject should continue ADT (e.g., if the subject is receiving clinical benefit).

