## Laboratory Testing

Each subject will have a “baseline” PSA value which must be the value obtained just prior to the MRI-TB which provided the initial histopathologic diagnosis. If the MRI-TB which initially diagnosed the subject’s PCa was obtained greater than 3-months from the time of study consent then a repeat PSA should be completed for screening to obtain a “baseline” PSA (unless one has been obtained for SOC at least 3-months after this initial biopsy in which case no repeat value is needed and this may be used for eligibility). This applies to all participants regardless of GG used for eligibility.

Baseline serum testosterone levels can be obtained at the time of the screening visit along with other screening labs if the patient does not have serum testosterone levels within 3-months of screening.

In addition to baseline, PSA and serum testosterone testing results will be collected for research purposes 8-weeks after initiation of neoadjuvant therapy and at 3-, 6-,9- and 12-months clinic visit following FT per SOC (see study calendar). The PSA values obtained at these timepoints are collected for SOC at normal clinical visits. After the 12-months study follow-up visit, patients will be followed-up on a schedule per SOC intervals.

If a subject shows an increase in PSA (>2 ng/mL higher than baseline PSA) at 8-weeks after initiation of neoadjuvant therapy, he will be considered to have biochemical progression and will be withdrawn from the study. He will be offered clinical care based on re-staging work-up per SOC.

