## Focal Therapy Procedure Combination with Androgen Deprivation therapy

Partial ablation of the prostate, although not considered to be standard among the intermediate- to risk PCa population, is a PCa management option for men interested in undergoing this treatment modality following the shared decision-making process with a urologist. Importantly, the description of the FT procedure that follows does not differ from partial ablation of the prostate provided for PCa patients as part of clinical care and is not considered in and of itself to be altered or changed in any way for research purposes.

Within 8- to 12-weeks of initiation of ADT, FT will be performed. The volume of tissue treated will be determined based on the discretion of the treating investigator, and as indicated according to the subject’s MRI-TB results at the time of his PCa diagnosis.

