# DURATION OF TREATMENT, FOLLOW-UP & WITHDRAWALS

## Duration of Therapy

In the absence of treatment delays due to adverse event(s) (AE), treatment may continue per protocol until one of the following criteria applies:

- Disease progression
- Intercurrent illness that prevents further administration of treatment
- Unacceptable AE(s)
- Patient decides to withdraw from the study treatment
- General or specific changes in the patient's condition render the patient unacceptable for further treatment in the judgment of the treating investigator
- If a subject shows an increase in PSA (>2 ng/mL higher than baseline PSA) at 8-weeks after initiation of neoadjuvant therapy, he will be considered to have biochemical progression and will be withdrawn from the study.
- Patient non-compliance
- Termination of the study by University of Chicago PI

The reason(s) for protocol therapy discontinuation, the reason(s) for study removal, and the corresponding dates must be documented in the study EDC (REDCAP) and within study source documentation.

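### The set labelled ITT leaves out men who receive ADT but never reach focal therapy, and no any-dose safety set exists, so the primary safety endpoint has the wrong denominator

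*Protocol*

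**What the plan says.** Section 13.6 (Analysis of Primary and Secondary Endpoints) states: "The ITT population includes all subjects who were enrolled and treated with the combination treatment (ADT (any duration) + FT". It continues: "The ITT population will serve as the primary analysis set for all safety and efficacy endpoints". The per-protocol set carries the same ADT-plus-FT condition and further excludes major deviations. No other population is defined.

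Other sections show that men can be treated and still fall outside this set:

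- **Timing.** Section 8.4: "Within 8- to 12-weeks of initiation of ADT, FT will be performed".
- **Loss of FT candidacy.** Section 6.5 deals with "Any subject who has already received ADT and who for any reason is no longer a candidate for FT". It classes him as a withdrawal "from treatment rather than a screen-failure".
- **PSA rise.** Under Section 8.2, if PSA at week 8 is more than 2 ng/mL above baseline, "he will be considered to have biochemical progression and will be withdrawn from the study". Section 10.1 repeats this.
- **Other exits.** Section 10.1 also lists unacceptable adverse events, disease progression, patient decision and "Intercurrent illness that prevents further administration of treatment".

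Section 6.2 dates a patient as on study from first treatment in a non-randomized trial, which here means the first ADT dose. Section 13.6 also notes: "Subjects who are enrolled but not treated will be documented as screen failures".

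**The concern.** Membership of the analysis set depends on what happens during the first part of the regimen under test. A man whose adverse event on ADT rules out surgery is exposed to study treatment but missing from the safety analysis. A man whose PSA rises on ADT is, in the protocol's own terms, a progression, but he is missing from the efficacy analysis. An intention-to-treat label tells readers that no such selection has taken place.

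Safety of the combination is a primary objective (Section 3.1) and a primary endpoint (Section 13.1), so the denominator of a primary result is at stake. The missing-data rule does not bring these men back: it imputes as positive only a biopsy missing after ablation, and they had no ablation.

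**Working it through.** **Following one man through the rules.** He starts ADT, so he is on study (Section 6.2). His adverse events are collected from consent (Study Calendar, footnote on AEs). He leaves before FT under Section 6.5, 8.2 or 10.1. He has not received ADT plus FT, so he is outside both the ITT and per-protocol sets (Section 13.6). There is no third set. This needs no arithmetic.

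**The plan's own figure.** Section 13.4 uses null 0.30, alternative 0.15, alpha 0.05 and power of at least 80%. The one-sample normal approximation is n = [(z_alpha × √(p0 q0) + z_beta × √(p1 q1)) / (p0 − p1)]².

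- One-sided: [(1.645 × √0.21 + 0.842 × √0.1275) / 0.15]² = 49.4, so 50. The stated 51 is within one patient of this.
- Two-sided, the formula gives 63.9, so 64. The stated figure therefore fits a one-sided test.
- Attrition: 51 / 0.90 = 56.7, so 57, as stated.

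The planned size is not the issue here. It supplies the scale for the illustrations.

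**Safety illustration.** Pre-FT losses are not given in the documents, so k is an assumption from 0 to 6, where 6 is the difference between 57 and 51. The safety denominator is then 57 − k instead of 57. In the extreme case where all 6 left for an adverse event on ADT, 6/57 = 10.5% of exposed men had a treatment-ending event before FT, and the primary safety set shows 0/51. With k = 0 there is no difference.

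**Efficacy illustration.** Assume 6 of 57 starters are lost before FT and 8 of the 51 treated men have a positive biopsy. Let d of the 6 be disease-related and counted as failures, with the other 6 − d counted as non-failures. The all-starter proportion is (8 + d)/57, with exact (Clopper-Pearson) 95% intervals:

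| Set | Failures / N | Proportion | 95% CI | Is 30% inside? |
|---|---|---|---|---|
| FT-treated | 8/51 | 15.7% | 7.0–28.6% | no |
| All starters, d = 0 | 8/57 | 14.0% | 6.3–25.8% | no |
| d = 1 | 9/57 | 15.8% | 7.5–27.9% | no |
| d = 2 | 10/57 | 17.5% | 8.7–29.9% | no |
| d = 3 | 11/57 | 19.3% | 10.0–31.9% | yes |
| d = 6 | 14/57 | 24.6% | 14.1–37.8% | yes |

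The estimate moves in either direction, and 30% enters the interval only from d = 3 upward.

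**Power if the all-starter composite were made primary.** The exact one-sided test on 57 men rejects 30% at 11 or fewer failures (actual alpha 0.0486). With k losses all counted as failures and a 15% rate in the rest, power is P(X ≤ 11 − k) with X binomial(57 − k, 0.15). This gives 86.2% for k = 0, 57.8% for k = 3 and 20.3% for k = 6.

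**The case against.** The strongest case for the current set concerns efficacy. The biopsy endpoints are defined at 12 months following FT (Section 13.1), and the 30% benchmark is for men who undergo FT (Section 13.4). An FT-treated denominator matches both. Counting PSA progression or inability to receive FT as failure creates a composite, and the 30% null was not set for that composite. This stands. A reader might infer that all ADT starters must replace the primary efficacy set, but the documents do not support going that far. The power figures show that such a switch would also require the null and the sample size to be revisited. The argument does not extend to safety, where nothing in the design justifies dropping exposed men.

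Four other stronger readings also fail:

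- **That harms before FT go unreported.** They do not. Adverse events are collected from consent, serious ones are expedited (Section 14.5), the monitoring committee reviews toxicity at least quarterly (Section 16.3), and all events are summarized in the final report (Section 14.2). The fault is confined to the primary safety analysis.
- **That the screen-failure note contradicts Section 6.5.** If untreated means no protocol therapy at all, the note agrees with Sections 6.1, 6.2 and 6.5. If it means the combination was not given, it conflicts. It is an ambiguity that could lead sites to misclassify exposed men.
- **That the set requires completed FT.** Section 13.6 speaks only of treatment with FT. The status of a started but unfinished procedure is not stated.
- **That the men lost are mostly ADT toxicities or progressions.** No frequencies are given. Section 6.5's own examples are anatomy, withdrawn consent and infeasibility.

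**Conclusion.** The point holds, in two parts of different weight. For safety, the plan is wrong as written: the primary analysis omits every man exposed to ADT who did not reach FT, and this must be corrected. For efficacy, the set is mislabelled and selected on events after treatment start, but it remains a defensible primary set for the biopsy endpoint if it is named for what it is and accompanied by an all-starter analysis.

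The size is unknown because it depends on the number of and reasons for pre-FT losses, neither of which the documents give. Under the assumed 6 losses of 57 and 8 failures of 51, the all-starter result ranges from 14.0% to 24.6% against 15.7% in the FT-treated set. The upper end requires all of the assumed attrition to fall before FT and all of it to be disease-related, so it is a bound, not an expectation. With no pre-FT losses, the two sets coincide and nothing changes.

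**What to change.** 1. Define the safety set as every man who received at least one dose of ADT, and use it for the primary safety endpoint.
2. Rename the current set FT-treated (modified ITT) and keep it for the primary biopsy endpoint. State whether a started but incomplete FT counts as treated.
3. Report the number of men lost before FT, by reason. Add a sensitivity analysis in all ADT starters that counts 8-week PSA progression and disease-related inability to receive FT as failures. Specify in advance how other pre-FT losses (adverse event, withdrawn consent) are counted, and note that the 30% null is not matched to this composite.
4. Clarify in Section 13.6 that enrolled but not treated means no ADT was given, in line with Section 6.5.

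The cost is wording and one or two extra tables. Adverse events, withdrawals and reasons for discontinuation are already recorded. The sensitivity estimate may be less favourable than the primary one. The sample size need not change, because the primary biopsy analysis stays on the FT-treated set.

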## Prostate Cryoablation and High-Intensity Focused Ultrasound Ablation for Focal Therapy Treatment of Prostate Cancer

Cryoablation, or tissue destruction by freezing, has been used as an alternative to surgical resection for decades.^5-8^ Cryoablation of the entire prostate has shown durable results for primary treatment and utilized as salvage treatment after primary RT for PCa.^9^ Studies of FT cryoablation have demonstrated a reduced rate of urinary incontinence and >80% preservation of erectile function.^10^ Oishi et al.^11^ prospectively evaluated 160 men who underwent cryoablation of localized PCa for oncologic and functional outcomes. Their primary endpoint was treatment failure-free survival, which was defined as requiring any radical and or whole gland treatment, initiation of systemic therapy, biochemical failure (increase of 2 ng/mL above the PSA nadir) or PCa specific mortality. Twenty-five men (16%) had high-risk PCa, 106 men (66%) had intermediate-risk and 29 men (18%) had low-risk PCa with an overall median baseline PSA of 6.3 ng/mL and follow-up of 40-months. Of note, 28 patients (17 intermediate-risk and 11 high-risk) received neoadjuvant ADT prior to FT for a median of 12-months. Transrectal ultrasound guided prostate biopsy was recommended at 1-year after FT cryoablation; however, 104 men ultimately underwent post-procedural prostate biopsy. The authors estimated that 5-year treatment failure-free survival, metastasis-free survival, cancer specific and overall survival were 85%, 100%, 100% and 100%, respectively. The 5-year CSPCa, i.e., GG ≥2, free survival was 87%, 74% and 64% for low-, intermediate- and high-risk subjects who underwent a post-procedural biopsy, respectively. Continence and potency were reported in 97% and 73% of patients, respectively, within 2-years of FT.

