## Sample Size/Accrual Rate

It is estimated that the 30% of men who undergo FT for intermediate-risk PCa will have CSPCa (GG ≥2) on repeat biopsy after FT. We hypothesize the combination of ADT, and FT will halve the proportion of men with residual or recurrent CSPCa to 15%. Using sample size estimates for a single proportion, comparing a null proportion of 0.30 to an alternative proportion of 0.15, with an alpha = 0.05 and power at least 80%, the total number of patients required will be 51 men. We estimate 10% attrition for a total sample size of 57 men. We are expecting 18-21 months to enroll all the patients and 36-months to complete the study.

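### The claim of at least 80% power ignores the rule that counts a missing post-ablation biopsy as positive, so it fails to the extent that attrition occurs after focal therapy

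*Protocol*

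**What the plan says.** The Protocol's Sample Size/Accrual Rate section takes 30% as the share of men who "will have CSPCa (GG ≥2) on repeat biopsy after FT" and hopes to halve it. The method is named only as a one-proportion estimate, at a 5% significance level and with 80% power or more. The hypotheses are set by "comparing a null proportion of 0.30 to an alternative proportion of 0.15". From these inputs the section finds that "the total number of patients required will be 51 men". On losses, its only statement is this: "We estimate 10% attrition for a total sample size of 57 men". It does not give sidedness, the test, or when the attrition is expected.

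The Analysis of Primary and Secondary Endpoints section defines the intent-to-treat set as men who were enrolled and received both ADT (any duration) and FT, and makes it the primary set for efficacy. Under Missing Data, for the primary analysis, "subjects with missing biopsy information post-ablation will be imputed as" positive when the proportion negative for clinically significant cancer is calculated. That proportion is the complement of the primary endpoint. The same section then expresses the primary result over the total number of patients, with a 95% confidence interval.

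**The concern.** Dividing 51 by 0.9 protects power only if the men lost drop out of numerator and denominator alike, leaving 51 men with a biopsy-based result at the assumed 15%. Under the imputation rule, a treated man without a biopsy stays in the denominator and is added to the numerator. The analysed rate then moves from 15% towards 30% for a reason unrelated to treatment effect. The 30% comparator is described as a rate on repeat biopsy, with no such penalty stated.

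This is a single-arm trial whose efficacy result is one proportion set against an external benchmark. A few missed biopsies could make a regimen that truly halves residual disease look much less effective, while readers are told that power is at least 80%.

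**Working it through.** **Inputs.** From Sample Size/Accrual Rate: p0 = 0.30, p1 = 0.15, alpha 0.05, power at least 80%, 51 men, 10% attrition, 57 in total. From Analysis of Primary and Secondary Endpoints: the treated-only primary set and missing counted as positive. Assumption: one-sided alpha, because the protocol does not state it.

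**Step 1: reproduce the plan's figure.** The normal approximation for one proportion, one-sided, is

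n = [(1.645 × √(0.30 × 0.70) + 0.842 × √(0.15 × 0.85)) / 0.15]² = 49.4, so 50.

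This is close to 51, and normal-approximation power at 51 is 81.3%. The same formula two-sided gives 64, so one-sided is the reading that fits. Inflation: 51 / 0.9 = 56.7, so 57. The stated design is therefore approximately reproduced, provided that lost men leave the analysis.

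**Step 2: the expected analysed rate under the imputation rule.** With a share f of treated men unbiopsied and a true rate of 15% among the others, the expected rate is 0.15 × (1 − f) + f. At f = 0.10 it is 0.135 + 0.10 = 0.235. It reaches 0.30, the null value, at f = 0.15 / 0.85 = 17.6%.

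**Step 3: power with 57 treated men.** The exact one-sided 5% rule at n = 57 rejects with 11 or fewer positives (size 0.0486). With m men imputed positive, power is P(X ≤ 11 − m), where X is binomial with 57 − m men and p = 0.15. The last column uses 10 or fewer positives (one-sided size 0.0241), a stand-in for requiring the 95% interval to lie below 30%.

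| Missing biopsies | Power, one-sided 5% | Power, 95% interval below 30% |
| --- | --- | --- |
| 0 | 86% | 77% |
| 1 | 79% | 67% |
| 2 | 69% | 56% |
| 3 | 58% | 43% |
| 6 | 20% | 10% |
| 10% at random | 28% | 18% |

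**Step 4: timing of the losses.** Suppose six of 57 enrolled men are lost (57 − 51 = 6) and k of them go before FT. The primary set is then 57 − k, with 6 − k imputed positive. In each row 51 men have a biopsy, and the critical value is recalculated for the size of the primary set.

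| Lost before FT | Treated, no biopsy | Primary set | Reject at or below | Power, one-sided 5% |
| --- | --- | --- | --- | --- |
| 0 | 6 | 57 | 11 | 20% |
| 2 | 4 | 55 | 10 | 34% |
| 3 | 3 | 54 | 10 | 50% |
| 4 | 2 | 53 | 10 | 65% |
| 6 | 0 | 51 | 9 | 77% |

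The last row is the design the sample-size section assumes. Its 77% against 81% is the gap between the exact test and the normal approximation and has nothing to do with imputation.

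**The case against.** A reader might infer that the sample size and the imputation rule cannot both hold, and that power is simply 20% to 28%. The documents do not support that. The 57 is a recruitment goal, and the protocol names exits between ADT start and FT: a PSA rise at 8 weeks (Laboratory Testing; Duration of Therapy), and FT that is infeasible or declined (Subjects who do not undergo Focal Therapy or complete Focal Therapy). Those men are outside the primary set and are never imputed. If all the attrition were of this kind, the two sections would agree. The 20% to 28% is the extreme case, in which every lost man was treated and has no biopsy.

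Three further points stand:

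- The section on post-FT efficacy and surveillance lets other post-treatment biopsies count, so fewer men will lack biopsy information than miss the 12-month visit.
- The cited cryoablation series, in which biopsy was recommended at one year, "however, 104 men ultimately underwent post-procedural prostate biopsy" out of 160 (35% without one), does not forecast this trial. Here the 12-month biopsy is a scheduled procedure, and men judged unlikely to comply are excluded. The series shows only that missed biopsies are a real prospect.
- The protocol states no success rule, so the cutoffs above are constructions used to evaluate its own power claim. It cannot be said that the trial would be reported as failing.

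It may also be said that missing counted as positive is a conservative, pre-specified rule that cannot flatter an uncontrolled regimen. That is a fair reason to keep it, and a reader should not infer that a complete-case primary analysis is needed. Such an analysis assumes that missing biopsies are uninformative, and on 51 men it has 77% exact power, also short of 80%. None of this rescues the stated power, which makes no allowance for the rule.

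**Conclusion.** The point holds in conditional form. The sample-size section treats the 10% as leaving the analysis, while the primary analysis counts treated men without a biopsy as positive. To the extent that attrition falls after FT, the claim of at least 80% power is wrong. One missing biopsy among 57 treated men already gives 79%, and three give 58%. For six losses in all, power runs from about 20% to 77% according to their timing, which the protocol leaves open. At 10% missing, the expected analysed rate is 23.5% instead of 15%, set against an unadjusted 30%.

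These figures assume a true rate of 15% among biopsied men, a one-sided 5% exact test, and no substitute biopsy for the men counted as missing. If success required the 95% interval to lie below 30%, every figure would be lower.

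**What to change.** In Sample Size/Accrual Rate:

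- Split the assumed 10% attrition into losses before FT and treated men with no post-FT biopsy.
- State the sidedness and the test.
- Replace the claim of at least 80% power with the power that the missing-as-positive rule gives over a plausible range of missing biopsies, such as the tables above.

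In Analysis of Primary and Secondary Endpoints, keep missing counted as positive as the pre-specified primary rule if the sponsor prefers it. Add, as a named supportive analysis, the proportion among FT-treated men with any post-FT biopsy, and report the number imputed beside the primary result, so that missed biopsies are not read as treatment failure.

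The cost is wording in two sections, one extra analysis and a less favourable stated power. No extra patients are needed to make the correction. The supportive analysis assumes that missing biopsies are uninformative, which is why it sits beside the primary rule and need not replace it.
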